**Table 3 Summary of published radiation exposure figures to staff during  $^{18}\text{F}$ -FDG guided surgery**

| Publication        | Injected activity of $^{18}\text{F}$ -FDG (MBq) | Time from injection to surgery (mins) | Time in operating room (Exposure time) (mins) | Mean dose equivalent per hour ( $\mu\text{Sv/h}$ ) |                       |              |
|--------------------|-------------------------------------------------|---------------------------------------|-----------------------------------------------|----------------------------------------------------|-----------------------|--------------|
|                    |                                                 |                                       |                                               | Surgeon                                            | Nurse / theatre staff | Anaesthetist |
| Nalley et al.      | 287.5                                           | 228                                   | Not reported                                  | 37.5                                               | 9.3                   | 2.0          |
| Povoski et al.     | 699                                             | 179                                   | 235                                           | 61                                                 | 17                    | 49           |
| Heckathorne et al. | 353                                             | 79                                    | (48.5 - surgeon)
(85.5 - nurse)            | 23                                                 | 10.5                  | NR           |
| Piert et al.       | 44                                              | 222.5                                 | 247.5                                         | 5.55                                               | 0.8                   | NR           |
| Andersen et al.    | 45                                              | 65                                    | 15 – 450                                      | 13.2                                               | 2.7                   | NR           |

### 7.2.7. Benefits to Participants

This study offers the potential benefits of more complete cancer detection and surgery to participants. The data collected in this study may also potentially provide benefits for future patients by informing the further development of the LightPath® Imaging System for the intraoperative assessment of tumour margins and lymph node involvement.

### 7.3. Study Population

Women  $\geq 18$  years of age with invasive breast cancer scheduled for primary breast-conserving surgery with or without sentinel lymph node biopsy (SLNB) or axillary lymph node dissection (ALND).

### 7.4. Inclusion Criteria

- Female subjects  $\geq 18$  years of age with a diagnosis of invasive breast cancer scheduled to undergo BCS
- Subjects who are able to give voluntary, written informed consent to participate in this study
- Subjects who are able to understand this study and are willing to complete all the study assessments

- Female subjects of childbearing age must have a negative pregnancy test (by Beta human chorionic gonadotrophin ( $\beta$ -HCG) qualitative analysis) or must have had a history of a surgical sterilisation or must give history of no menses in the past twelve months.

## 7.5. Exclusion Criteria

- Subjects who have had surgery to the ipsilateral breast in the past 12 months
- Subjects who have had radiotherapy to the ipsilateral breast
- Subjects who have a known hypersensitivity to  $^{18}\text{F}$ -FDG
- Subjects who are pregnant or lactating
- Subjects who have an existing medical condition that would compromise their participation in the study.

## 8. Study Procedures

### 8.1. Study Start and Training

The study will not commence until all the necessary approvals are in place and a formal initiation visit has taken place.

At the initiation visit, the PI will ensure that all study personnel are fully aware of all the study requirements.

### 8.2. Recruitment

Female patients  $\geq 18$  years of age with a diagnosis of invasive breast cancer, and scheduled to have breast conserving surgery (BCS) with or without SLNB or ALND, will be screened for enrolment in the study at the Breast Multidisciplinary Team Meetings (MDM) according to the criteria listed in sections 7.4 and 7.5 of this protocol. A member of the research team will then approach the patient, at the time of their clinical hospital visit, should the situation and the patient's emotional status allow it. Patients who display an interest in participating will be provided with a copy of the Patient Information Sheet (PIS). Patients who have been provided with the PIS will be approached by a member of the research team at their next visit or receive a telephone call to answer any questions that may arise. Patients are then invited to participate in the study, and informed consent will be obtained as outlined in section 8.3.

### 8.3. Informed Consent

Potential participants will be provided with written information concerning the study, advising them of the study requirements, and possible risks. Appropriately qualified healthcare staff trained in this protocol and GCP will ensure that potential participants understand the information provided, and review requirements and potential risks. Potential participants will have at least 48 hours in which to review this information.

Each subject will be informed that participation in the study is voluntary and non-participation will not affect their care. Subjects are free to withdraw from the study at any time irrespective of their initial consent.

Each subject will also give their permission for representatives of the Sponsor, auditor and regulatory authorities to review their hospital records for the purposes of source data verification.

Individuals agreeing to participate in the study will sign an informed consent form approved according to local regulations. All signed consent forms will be maintained in the investigator site file at the study site and a copy provided to the subject. Upon verification of eligibility and execution of informed consent, subjects will be assigned a unique identification code number, which will be used to identify the subject and maintain anonymity of personal data.

#### **8.4. Baseline Data**

Relevant demographic data, e.g., age, height and weight will be collected, the medical history, including the diagnosis for which surgery is indicated, tumour characteristics, e.g., size, grade, receptor status, focality, and any lymph node involvement will be recorded.

If a participant fails to fulfil any element of the inclusion and exclusion criteria, this will be documented and the signed consent form and completed inclusion/exclusion criteria retained by the Investigator. The participant will not be advanced any further in the study.

#### **8.5. Concomitant Medication/Treatments**

No concomitant medication and/or treatments will be withheld for any subject participating in this study. All concomitant medication and/or treatments will be recorded.

#### **8.6. Day of surgery**

##### **8.6.1. Radiopharmaceutical administration**

Prior to her surgery, the participant will be prepared for surgery in accordance with the local hospital standard of care. The following information/procedures will be completed on the day of surgery or the day before surgery by a designated team trained in administering radiopharmaceuticals:

- Administration of  $^{99m}\text{Tc}$  tracer prior to the administration  $^{18}\text{F}$ -FDG
- Administration of  $^{18}\text{F}$ -FDG.

Administration of  $^{18}\text{F}$ -FDG will be scheduled accordingly, to ensure the LightPath® images will be taken approximately 145 minutes post-injection of  $^{18}\text{F}$ -FDG.

Work-up and preparation for surgery will be performed as per standard of care.

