## 2.4. Schedule of Events

| Procedures                                                                          | Screening | Day of Surgery | Discharge | Study Completion at MDT decision on re-operation (1-2 weeks) |
|-------------------------------------------------------------------------------------|-----------|----------------|-----------|--------------------------------------------------------------|
| Visit                                                                        | 1  | 2       | 2  | 3                                                     |
| Informed Consent                                                                    | X         |                |           |                                                              |
| Inclusion/Exclusion                                                                 | X         |                |           |                                                              |
| Demographics, Medical History                                                       | X         |                |           |                                                              |
| Biomarkers (ER/PR/HER2/other, according to local practice)                          | X         |                |           |                                                              |
| Injection of 99m Tc                                                      |           | X              |           |                                                              |
| Injection of  F-FDG                                                    |           | X              |           |                                                              |
| Standard-of-care surgical procedure                                                 |           | X              |           |                                                              |
| Intra-operative specimen x-ray analysis of WLE specimen as per standard-of-care     |           | X              |           |                                                              |
| LightPath® imaging of WLE specimen                                                  |           | X              |           |                                                              |

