### 7.2.4. Radiation exposure associated risks from $^{99\text{m}}\text{Tc}$ -nanocolloid

SLNB is currently routinely performed on breast cancer patients undergoing WLE who are clinically and radiologically lymph node negative. The procedure may vary between institutions, but is typically performed using 'the combined technique'. An

injection of 20 - 40 MBq of Technetium 99m ( $^{99m}\text{Tc}$ ) tracer is given pre-operatively, and/or blue dye is injected intraoperatively. The SLNs are localised using a handheld gamma probe (such as Europrobe 3, Euromedical Instruments, Le Chesnay, France) and/or visually (i.e., blue discolouration).

In this study, the presence of  $^{18}\text{F}$ -FDG will result in a greater than normal background signal being detected by the handheld gamma probe, potentially masking low activity SLNs.

To mitigate the risk of  $^{18}\text{F}$ -FDG interfering with gamma probe detection of SLNs, the administered activity of  $^{99m}\text{Tc}$  tracer for SLNB can be increased to up to 40 MBq as a one-day protocol for SLNB. Furthermore, a collimator will be attached to the gamma-probe, to block perpendicular gamma photons and allow for directional detection of SLNs. With this administered activity and the addition of a collimator, the  $^{99m}\text{Tc}$  signal in the SLN has been shown to be sufficient to allow clear differentiation of the SLN from the  $^{18}\text{F}$ -FDG background signal. The increased dose of 150 MBq allowed successful SLNB in all subjects in the clinical study of LightPath® in breast cancer conducted at Guy's Hospital in London, UK (LPM-001, ClinicalTrials.gov Identifier NCT02037269). A multicentre trial in Poland showed that a successful SLNB procedure may be achieved with an injected  $^{99m}\text{Tc}$  activity as low as 37 MBq (LPM-007, ClinicalTrials.gov Identifier: NCT02666079) (Jurrius et al., 2021).

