### 8.6.3. BCS plus axillary surgery (SLNB or ALND)

Participants scheduled to have BCS plus SLNB will receive  $^{99\text{m}}\text{Tc}$  and  $^{18}\text{F}$ -FDG.  $^{99\text{m}}\text{Tc}$  will be injected in the peri-areolar region and  $^{18}\text{F}$ -FDG administered intravenously in the Nuclear Medicine Department, approximately 145 minutes prior to CLI + FAR LightPath® imaging. Blue dye might be injected intraoperatively according to the local protocol; BCS and axillary surgery will be performed as per standard of care. In patients undergoing an SLNB, a collimator attached to the gamma-probe will allow directional detection of lymph nodes and shield the probe from  $^{18}\text{F}$ -FDG activity from the main tumour. Imaging procedures of the WLE specimen will be as described in section 8.6.2.

Sutures and surgical clips will be placed on the WLE specimen to record the anatomical orientation, as per standard practice. Based on the information on the LightPath® images additional sutures may be used to allow precise mapping between the histopathological analysis and CLI + FAR LightPath® imaging. Information on the surgical procedure will be recorded on the study case report form (CRF).

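### Section 8.6.1 allows the 99mTc tracer to be given the day before surgery, against the Schedule of Events and the one-day protocol in Section 7.2.4

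*Protocol*

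**What the plan says.** Section 8.6.1 of the protocol sits under the heading "8.6. Day of surgery". It states that the items listed there "will be completed on the day of surgery or the day before surgery", by a team trained in giving radiopharmaceuticals. The list has two items: the 99mTc tracer, to be given before FDG, and FDG itself. The same section then requires FDG to be scheduled so that imaging falls about 145 minutes after injection.

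Three other places bear on when 99mTc is given:

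- **Section 2.4, Schedule of Events.** The row "Injection of 99m Tc" is marked under the day of surgery only. The table has no day-before column.
- **Section 7.2.4.** FDG raises the background seen by the gamma probe and may hide low-activity nodes. To counter this, the activity of the "tracer for SLNB can be increased to up to 40 MBq as a one-day protocol for SLNB", and "a collimator will be attached to the" gamma probe. Given that activity and the collimator, the section says the 99mTc "signal in the SLN has been shown to be sufficient to allow clear differentiation of the SLN from the" FDG background.
- **Section 8.6.3.** For patients having sentinel lymph node biopsy (SLNB), 99mTc is injected around the areola and FDG is "administered intravenously in the Nuclear Medicine Department, approximately 145 minutes prior to CLI + FAR" imaging. The section adds: "Blue dye might be injected intraoperatively according to the local protocol".

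Sections 4.2.1 and 4.2.2 limit 99mTc to 40 MBq, place it before FDG under standard of care, and give its half-life as 6.02 h.

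**The concern.** The text a nuclear medicine team would follow when booking the injection permits a timing that the Schedule of Events does not. It also departs from the only regimen the protocol describes for keeping nodes detectable above the FDG background. A team that read Section 8.6.1 literally could inject 99mTc the day before and then carry out SLNB with study FDG present, outside the one-day protocol of Section 7.2.4.

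What is at stake is the conduct and safety of SLNB in the participants who have it. The extra background exists only because of the study tracer, so the protocol should be clear about the measure that offsets it. The margin-status endpoint and its analysis do not depend on this point.

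**Working it through.** **Step 1: which tracer can the day-before option apply to?** The list in Section 8.6.1 contains only 99mTc and FDG. General surgical work-up has its own sentence in that section and is not part of the list. FDG is fixed at about 145 minutes before imaging (Sections 4.1.2, 8.6.1, 8.6.2 and 8.6.3). From 250 MBq and the 110-minute half-life in Section 4.1.2:

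- at 145 min: 250 × 2^(−145/110) ≈ 100 MBq
- at 18 h (an assumed day-before interval): 250 × 2^(−1080/110) ≈ 0.3 MBq

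FDG given the day before would break the timing rule and leave almost nothing to image. The option therefore has effect only for 99mTc.

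**Step 2: compare the texts.**

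| Place | Timing of 99mTc |
|---|---|
| 8.6 heading | day of surgery |
| 8.6.1 | day of surgery or the day before |
| 2.4 | day of surgery only |
| 7.2.4 | one-day protocol, with collimator |
| 8.6.3 | not clearly fixed: the 145 minutes may attach to FDG alone |
| 4.2.2 | before FDG; no interval given |

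Nothing in the protocol reconciles the second row with the third and fourth, and no two-day regimen or activity is described anywhere.

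**Step 3: how much does the choice of day change?** The protocol gives no figure of its own to reproduce, and no interval from 99mTc injection to surgery. The intervals below are assumptions: 145 min (2.417 h) to 4 h for same-day injection, and 16 to 24 h for the day before. Inputs are the 6.02 h half-life and the 40 MBq cap (Section 4.2.2). The residual is A(t) = 40 × 2^(−t/6.02).

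| Interval t | Fraction left | Left from 40 MBq |
|---|---|---|
| 2.417 h | 2^(−2.417/6.02) = 0.757 | 30.3 MBq |
| 4 h | 2^(−4/6.02) = 0.631 | 25.2 MBq |
| 16 h | 2^(−16/6.02) = 0.159 | 6.3 MBq |
| 24 h | 2^(−24/6.02) = 0.063 | 2.5 MBq |

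Ratio of same-day to day-before residual:

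- smallest (4 h against 16 h): 0.6309 / 0.1585 = 3.98
- largest (2.417 h against 24 h): 0.7571 / 0.0631 = 12.0

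The ratio does not depend on the activity injected. Restoring the same residual after a day-before injection would take 40 × 3.98 ≈ 159 MBq up to 40 × 12.0 = 480 MBq, and the 40 MBq cap rules that out.

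**Step 4: what the figures do not show.** They describe residual injected activity. The protocol gives no nodal uptake, clearance or detection threshold, so they cannot be turned into a probability of missing a node.

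**The case against.** The strongest reply is that the protocol plainly intends same-day injection and that this is a slip of wording. The disputed phrase stands under a day-of-surgery heading. Section 8.6.3, the specific section for SLNB patients, describes both tracers in one sentence. FDG already brings every participant to Nuclear Medicine on the day, and no separate visit the day before is described. The point about intent stands, and it is the reason this is a wording inconsistency. It does not remove the conflict: Section 8.6.1 expressly permits the other day, and the 145 minutes in Section 8.6.3 can be read as applying to FDG alone.

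A second reply concerns Section 7.2.4. Its wording on activity is permissive, and its claim of sufficient signal names the activity and the collimator, not an interval. The studies it cites are likewise described by activity (150 MBq and 37 MBq), with no injection-to-surgery time. This is fair, and it makes the clash with Section 7.2.4 softer than the clash with the Schedule of Events. Even so, the one-day protocol is the only regimen offered as mitigation. An appeal to local standard of care does not settle the timing either, because Section 7.2.4 says that FDG raises the background above normal in this study.

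Third, the decay intervals are assumed and say nothing measured about node detection. That stands in full. The collimator is required whichever day is chosen, and blue dye may be used.

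**Conclusion.** Section 8.6.1 is wrong as written, and the matter is minor. The contradiction with the Schedule of Events, and with the one-day protocol in Section 7.2.4, follows from the text alone and needs no assumption. Its size, a residual 99mTc activity about 4 to 12 times lower, rests on the stated half-life, on assumed intervals of 2.4 to 4 h and 16 to 24 h, and on physical decay only. No claim is made that nodes would be missed. The correction is worth making because this is operative scheduling text that allows a practice at odds with a stated safety measure for SLNB participants.

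**What to change.** In Section 8.6.1, remove the day-before alternative for tracer administration, so that 99mTc is given on the day of surgery, before FDG. This agrees with Sections 2.4 and 7.2.4. FDG loses nothing, because the 145-minute rule already excludes the day before, and no other item in the list depends on the phrase.

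The cost is a one-phrase amendment and slightly tighter same-day scheduling in Nuclear Medicine. No procedure is added and no activity changes.

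The sponsor should confirm that same-day injection is what was meant. If the site does want to inject the day before, the protocol must describe and justify a two-day regimen in the presence of FDG, and Sections 2.4, 4.2.2 and 7.2.4 must be amended to match.

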### 8.6.2. BCS only

Participants scheduled to have BCS will be administered  $^{18}\text{F}$ -FDG intravenously in the Nuclear Medicine Department, approximately 145 minutes prior to CLI + FAR LightPath® imaging. BCS will be performed as per standard of care. Following resection, the WLE specimen and shavings (if any) will be examined intraoperatively using CLI + FAR LightPath® imaging. If the surgeons detect a positive signal, they will perform cavity shavings of the resection cavity area corresponding to the positive signal area. It will be at the surgeon's discretion to choose whether to act based upon the intraoperative LightPath® images.

### 8.6.3. BCS plus axillary surgery (SLNB or ALND)

Participants scheduled to have BCS plus SLNB will receive  $^{99\text{m}}\text{Tc}$  and  $^{18}\text{F}$ -FDG.  $^{99\text{m}}\text{Tc}$  will be injected in the peri-areolar region and  $^{18}\text{F}$ -FDG administered intravenously in the Nuclear Medicine Department, approximately 145 minutes prior to CLI + FAR LightPath® imaging. Blue dye might be injected intraoperatively according to the local protocol; BCS and axillary surgery will be performed as per standard of care. In patients undergoing an SLNB, a collimator attached to the gamma-probe will allow directional detection of lymph nodes and shield the probe from  $^{18}\text{F}$ -FDG activity from the main tumour. Imaging procedures of the WLE specimen will be as described in section 8.6.2.

Sutures and surgical clips will be placed on the WLE specimen to record the anatomical orientation, as per standard practice. Based on the information on the LightPath® images additional sutures may be used to allow precise mapping between the histopathological analysis and CLI + FAR LightPath® imaging. Information on the surgical procedure will be recorded on the study case report form (CRF).

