| Study Design        | Interventional, Open, Single Arm                                                                                                                                                                                                                                                                                                                                                                                                                                                                                                                                                                                                                                                                                                                                                                                                                                                                                                                                                                                                                                                                                                                                                                                                                                                                                                                                                                                                                                                                                                                                                                                                                                                                                                                                                |

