### 8.6.4. LightPath® assessment

The WLE specimen will be examined by CLI + FAR LightPath® imaging at the time of the surgical procedure. All LightPath® images will be performed within approximately 145 minutes post-injection of  $^{18}\text{F}$ -FDG. If imaging is delayed for any reason, the reason must be recorded on the CRF. Imaging must be performed without unnecessary delay and following the acquisition times set out in the IFU, in order to avoid any degradation in specimen quality prior to transfer to the tissue bank / pathology department for routine analyses.

The operating surgeon will interpret the recorded CLI + FAR LightPath® Images. It will be at the surgeon's discretion to choose how to act on the CLI + FAR LightPath® images.

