#### **8.6.8. Histopathological assessment**

The WLE specimens and cavity shavings will then be examined according to the standard of care histopathology analysis as per the routine pathway at Synlab, Histopathology laboratories, St. Thomas' Hospital. Details of tumour dimensions along with all other histopathology minimum dataset items will be recorded. The distance from the tumour to the radial margins (medial, lateral, superior, inferior, posterior and anterior) will be recorded.

For the histopathology central assessment of the WLE, margins are defined (Toss et al 2017) as either:

- Invasive carcinoma – positive <1mm; negative ≥1mm
- DCIS - positive: <2mm; negative ≥2mm

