### 11.7.1. Analysis of the Primary Outcome Measure

The primary outcome will be the diagnostic performance of intraoperative CLI + FAR LightPath® imaging, assessed using a confusion matrix to describe the relationship between the results of tumour margin assessment (positive or negative) with CLI + FAR LightPath® imaging and standard-of-care histopathology (positive or negative) (gold standard).

| Standard-of-care histopathology |          |       |
|---------------------------------|----------|-------|
| Positive                        | Negative | Total |

|                                    |          |        |        |     |
|------------------------------------|----------|--------|--------|-----|
| CLI + FAR
LightPath®
imaging | Positive | a (TP) | b (FN) | a+b |
|                                    | Negative | c (FP) | d (TN) | c+d |
|                                    | Total    | a+c    | b+d    | n   |

Sensitivity =  $a/(a+c)$

Specificity =  $d/(b+d)$

Overall agreement =  $(a+d)/(a+b+c+d)$

TP = true positive; FP = false positive; FN = false negative; TN = true negative

The primary outcome measures are sensitivity, specificity and overall accuracy.

The following diagnostic accuracy statistics will be presented (as a percentage together with 95% exact confidence intervals):

- Sensitivity - The proportion of subjects with positive margin confirmed by histopathology who have a positive result on LightPath® Imaging.
- Specificity - The proportion of subjects with clear margin confirmed by histopathology who have negative result on LightPath® Imaging.
- Overall accuracy - The proportion of subjects whose margin status is correctly classified by LightPath® Imaging
- Positive predictive value - The probability of positive margin in subjects with a positive result on LightPath® Imaging.
- Negative predictive value - The probability of clear margin in subjects with a negative result on LightPath® Imaging.
- Positive likelihood ratio (LR+) = sensitivity/1-specificity
- Negative likelihood ratio (LR-) = 1-sensitivity/specificity
- Diagnostic odds ratio (DOR) = (TP/FP)/(FN/TN)

As a sensitivity analysis, the primary analysis will be repeated using the ITT analysis set and for the combined per protocol set.

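### Sutures guided by the LightPath image, with no masking of the pathologist, may leave the reference standard dependent on the index test

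*Protocol*

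**What the plan says.** Section 8.6.3 describes two kinds of marking. The first is routine: "Sutures and surgical clips will be placed on the WLE specimen to record the anatomical orientation, as per standard practice". The second depends on the index test. On the strength of what the LightPath images show, the text continues, "images additional sutures may be used to allow precise mapping between the histopathological analysis and CLI + FAR" imaging.

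The order of events follows from the next sections. Section 8.6.4 places the reading of the images in theatre: "The operating surgeon will interpret the recorded CLI + FAR LightPath" images. Section 8.6.8 then says that the WLE specimens and shavings "will then be examined according to the standard of care histopathology analysis as per the routine pathway". It also requires that "The distance from the tumour to the radial margins (medial, lateral, superior, inferior, posterior and anterior) will be recorded", and sets cut-offs below 1 mm for invasive disease and below 2 mm for DCIS.

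The synopsis gives the design as "Interventional, Open, Single Arm" and names histopathology as the gold standard. Section 11.7.1 states: "The primary outcome measures are sensitivity, specificity and overall accuracy".

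The protocol nowhere says that the pathologist is unaware of the LightPath result or of what the extra sutures mean. It does not say that margin status is fixed before those sutures are used for mapping, or that image-negative sites are marked too.

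**The concern.** All three primary measures presuppose that the reference result is reached without knowledge of the test result. Here a trace of the test result can travel on the specimen to the person who sets the reference result.

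A suture shows where to look. Section 5.3 says the scintillating film responds to tumour up to about 3 mm from the surface, which is deeper than either histological cut-off. Whether an image-positive site counts as a true or a false positive can therefore turn on whether the closest focus lies in the block that was cut. Extra sections at a marked site can turn a false positive into a true positive, which raises sensitivity, specificity and accuracy together. An unmarked image-negative site gets no such second look, and disease missed there is counted as a true negative.

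This concerns specimen handling and reader masking. A statistical analysis plan could not undo it once the specimens have been reported.

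**Working it through.** The protocol states no figure on this point, so there is none to reproduce. The model below shows only direction and scale.

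**Inputs from the protocol (11.6.2):** prevalence of positive margins p = 0.20 (planned for histopathology, treated here as the true prevalence); planned sensitivity 95%; planned specificity c = 0.90; 54 analysable patients.

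**Assumptions, not in the protocol:** routine histopathology finds a share d = 0.6 to 0.8 of truly positive margins, equally for image-positive and image-negative sites. When sutures guide the work, every image-positive site is sutured and all disease there is found, while image-negative sites stay at d. A true sensitivity s of 80% is added to show how the effect grows.

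**Guided reading**
- TP = p·s
- FN = p(1−s)d
- FP = (1−p)(1−c)
- TN = (1−p)c + p(1−s)(1−d)
- Measured sensitivity = s / [s + (1−s)d]

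**Unguided reading**
- TP = p·s·d
- FP = (1−p)(1−c) + p·s(1−d)
- FN and TN as above
- Measured sensitivity = s

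**Sensitivity, guided**
- s = 0.95, d = 0.8: 0.95/(0.95 + 0.04) = 96.0%
- s = 0.95, d = 0.6: 0.95/(0.95 + 0.03) = 96.9%
- s = 0.80, d = 0.8: 0.80/(0.80 + 0.16) = 83.3%
- s = 0.80, d = 0.6: 0.80/(0.80 + 0.12) = 87.0%
- d = 1: measured sensitivity equals s, so there is no inflation

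**Specificity and agreement.** Per 1,000 units with s = 0.80 and d = 0.8:
- Guided: TP 160, FN 32, FP 80, TN 720 + 8 = 728. Specificity 728/808 = 90.1%; agreement 888/1,000 = 88.8%.
- Unguided: TP 128, FN 32, FP 80 + 32 = 112, TN 728. Specificity 728/840 = 86.7%; agreement 856/1,000 = 85.6%.

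The same steps for all four cases, where true specificity is 90% and true agreement is 91.0% (s = 95%) or 88.0% (s = 80%):

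| s | d | Sensitivity, guided / unguided | Specificity, guided / unguided | Agreement, guided / unguided |
|---|---|---|---|---|
| 95% | 0.8 | 96.0% / 95.0% | 90.0% / 86.0% | 91.2% / 87.4% |
| 95% | 0.6 | 96.9% / 95.0% | 90.0% / 82.3% | 91.4% / 83.8% |
| 80% | 0.8 | 83.3% / 80.0% | 90.1% / 86.7% | 88.8% / 85.6% |
| 80% | 0.6 | 87.0% / 80.0% | 90.2% / 83.6% | 89.6% / 83.2% |

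If only some image-positive sites are sutured, the effect is smaller. With half sutured, s = 0.95 and d = 0.8, the image-positive disease found is 0.95 × (0.8 + 0.5 × 0.2) = 0.855, and sensitivity reads 0.855/(0.855 + 0.04) = 95.5%.

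**Scale.** 0.20 × 54 = 10.8, so about 11 patients are expected to be histology-positive. One such patient moves patient-level sensitivity by 1/11, about 9 points.

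**The case against.** The strongest reply is that the mechanism is inferred. The sutures are optional, the sentence stands only in the section on BCS with axillary surgery, and it does not say that sutures mark positive sites only or that the pathologist is told their meaning. Section 8.6.8 sends every specimen through the same routine pathway and has all six margins measured against fixed cut-offs. A two-tier search of the specimen is written nowhere. All of this stands, and it limits how strongly the point can be put. It does not remove the point: measuring six distances fixes what is reported, not how intensively each face is sampled, and optional marking without a rule can be selective. Section 8.6.8 does speak of a central assessment, but does not say that it is masked.

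A second reply is that guidance may bring the result closer to the truth. In the table, guided specificity and agreement lie nearer the true values than the unguided ones, because unguided work misses disease under image-positive sites and books it as false positive. That is correct under these assumptions. But the declared comparator is standard-of-care histopathology. A reference that searches harder where the test was positive is a different comparator, and it flatters sensitivity.

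A third reply is that uniform sutures do not secure independence, because a LightPath-positive face can lead to a cavity shaving that also goes to pathology. This stands too. The signal is imperfect, since specimen x-ray can also prompt a shaving, but it remains.

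Finally, the roughly 360-margin analysis in 11.7.1 needs each signal assigned to the right face, which the sutures help with. Markers on every face would still serve that purpose.

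**Conclusion.** The protocol contains a stated procedure by which the reference standard may come to depend on the index test, and it states no safeguard. The three primary measures can be overstated relative to an independent reading, provided that the sutures are used, that they favour image-positive sites, that they change sampling or reading, and that routine sampling misses some close disease.

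A reader might infer that measured sensitivity is in fact inflated, or that the direction at least is certain. The text supports neither. In the model the effect on sensitivity is upward or nil: it is nil if routine sampling finds every positive margin, and nil if the sutures leave the pathologist's work unchanged. A reader might also take a bias of several points as the expected size. That figure belongs to a true sensitivity well below the planned one. At the planned 95% the illustration gives 1 to 2 points, less than the 9 or so points that one histology-positive patient carries. The detection shares are assumptions, and the true size cannot be derived from the protocol.

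The point is worth correcting because the bias is avoidable and falls on the primary endpoint. It does not invalidate the design.

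**What to change.** 1. In 8.6.2 and 8.6.3 alike, place the same mapping markers on all six faces of every WLE specimen whatever the LightPath result. Alternatively, if image-based sutures are kept, place matching sutures at image-negative sites.
2. In 8.6.8, state that the six WLE margin distances are reported without knowledge of the LightPath images or calls and, as far as practicable, before the cavity shavings are reviewed.
3. State that LightPath-histology mapping is done only after those distances are recorded.
4. Acknowledge as a limitation that shavings may still convey some information about the LightPath result.

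The cost is protocol wording, a few extra sutures per specimen and an agreed reporting order with the laboratory. Surgical decisions are unaffected. Spot-level mapping becomes slightly less exact. The sponsor should also expect that measured specificity and agreement may be lower than under guided reading if routine sampling misses close disease: in the illustration, specificity falls from about 90% to 82-87%.
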